This pilot study will also assess the feasibility of data collection methods and intervention implementation (recruitment, retention, intervention fidelity, acceptability, adherence to the intervention, and engagement) not only for the larger scale study but also in the view of the application of the intervention with people with more severe dementia or in rehabilitative units (Teresi et al., 2022). The feasibility assessment will be carried out by a senior researcher in the role of supervisor who will analyze the data collection method and the intervention implementation according to the guidelines provided by Teresi et al. (2022).

The study includes dementia care professionals (DCPs) (e.g., neuropsychologists, physicians, educators, nurses, professional caregivers), and older people with dementia (OPDs) that will be monitored in different phases, depending on the type of variable and instrument used. Some data will be analyzed by a pre-post group comparison. The data will be collected in three moments: one week before the start of the intervention (T0), at its end (T1), and 2 weeks after the end of the intervention (T2). Data will be also collected during the intervention phase and analyzed longitudinally depending on the time frame of the collection (daily from T0 to T2 versus at each SOUND session). The Figure 1 below shows the progression of the data collection and experimental phase within the Research design.

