### 2.2 Conditions

#### 2.2.1 Participants

In every study country, 15 OPDs and 15 DCPs will be recruited and participate to the experimentation, for a total of 45 OPDs and 45 DCPs (90 people overall). OPDs and DCPs’ inclusion and exclusion criteria are summarized below (Table 1).

**TABLE 1 T1:** Participants’ selection criteria.

Type of participants	Inclusion criteria	Exclusion criteria
OPDs	• Interest in the project and signed consent form • Age 65 + • To be able to see, hear and move • Diagnosis of MCI or dementia with mild to moderate impairment (MoCA total score ≥ 10/30) • Absence of aphasia (mild acceptable) • Be able to understand and undertake simple task as required during activities	•Lack of consent to participate • Age 65− • Not be able to see, hear and move even with the help of appropriate aids • Absence of formal diagnosis of MCI or dementia or severe level of impairment (MoCA total score ≤ 10/30) • Moderate to severe aphasia • Not able to understand and undertake simple task as required during activities
DCPs	• Having experience in the dementia field (e.g., educators, occupational therapists, physiotherapists, psychologist, sociologists, nurses, music therapists, professional caregivers, doctors) • Having interest in the project and signed consent form • For the (co-)facilitators and internal/external observers: having completed the SOUND training	• Lack of experience working in the dementia field • Lack of consent to participate • For the (co-)facilitators and internal/external observers: lack of completion of the SOUND training

Older people with dementias will be recruited from the study organizations, health care dementia services and community services such as diagnostic centers, dementia day care centers, residential care facilities and charities. Individuals will already have a formal diagnosis of MCI or dementia. Their level of cognitive impairment is routinely assessed by the health professionals of the organization to which they belong. Therefore, these health professionals will support the recruitment and selection processes. Ethical approval has been obtained depending on the national legal requirements. OPDs retention will be empowered by collaborating with their professional caregivers who will present the SOUND activities as a pleasant novelty and as a gift.

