### 2.3 Outcome measures and data collection tools

#### 2.3.1 Outcome measures

The primary outcome variable for OPDs is the level of their mental wellbeing, while the primary outcome variable for care professionals is the level of burnout. Secondary outcomes variables for DCPs are (a) level of stress, (b) level of work cooperation and of (c) emotional well-being and, for OPDs, they are levels of (a) cognitive abilities, (b) neuropsychiatric symptoms, (c) mood and (d) emotional well-being.

Pre, post and longitudinal-intervention outcome (Table 3) as well as live monitoring tools (Table 2) were developed for assessing the impact of the SOUND intervention on DCPs and OPDs.

**TABLE 3 T3:** Pre, post and longitudinal-intervention outcome tools.

Target group	Tools	Variables	Who administers the tool	Who answers the questions	When it is used
DCPs	Burnout Assessment Tool (BAT)	Stress	Care professional	Care Professional	T0, T1, T2
	*Ad hoc* questionnaire	Stress	Care professional	Care professional	T0, T1, T2
	*Ad hoc* questionnaire	Work cooperation	Care professional	Care professional	T0, T1, T2
	Longitudinal Emotional Well-being thermometer (LEWT)	Emotional wellbeing	Care professional	Care professional	Daily report from T0 to T2
OPDs	Neuropsychiatric Inventory (NPI)	Neuropsychiatric symptoms (patient) and Caregiver Distress	Psychologist	Family caregiver	T0, T1, T2
	MoCA	General cognition	Psychologist	Older person	T0, T1, T2
	FAB	Cognition – Executive functions	Psychologist	Older person	T0, T1, T2
	HADS	Mood	Psychologist	Older person	T0, T1, T2
	WHO (Five) Well-Being Index (WHO-5)	Wellbeing	Psychologist	Older person	T0, T1, T2
	Longitudinal Emotional Well-being Thermometer (LEWT)	Emotional wellbeing (of patient)	Family caregiver	Family caregiver	Daily report from T0 to T2

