#### 2.3.2 Pre-post and longitudinal tools

Concerning DCPs, an *ad hoc* questionnaire has been developed to investigate the level of stress and cooperation of professionals before and after the intervention. Beyond the demographic questions (i.e., age, gender, nationality, marital status, education), the pre-intervention questionnaire includes *ad hoc* questions on: (a) work condition (e.g., position, role, activities); (b) music attitudes; (c) well-being, motivation, satisfaction and self-realization at work (d) teamwork, (e) relationship with patients and family caregivers. Additionally, the Burnout Assessment Tool (BAT) will be administered for evaluating the work-related stress. Respondents can answer all the questions (i.e., both *ad hoc* questions and the BAT battery) through a five-point Likert scale, where 1 represents the lower and 5 the higher score/frequency. The post-intervention questionnaire for DCPs follows the same structure of the pre-intervention ones, except for quantitative and qualitative questions asking to what extent and how the intervention has improved every area e.g., well-being, team work, relationship with OPDs.

The Burnout Assessment Tool (BAT) is a self-assessment questionnaire that measures parameters associated with burnout (De Beer et al., 2020; Schaufeli et al., 2020) validated in Italy (Angelini et al., 2021; Borrelli et al., 2022), in Romania (Oprea et al., 2021), in Portugal (Sinval et al., 2022) and with European cut-off scores (Schaufeli et al., 2023). The BAT contains four different subscales: exhaustion, mental distance, loss of emotional control and loss of cognitive control. In addition, there are two sub-dimensions: psychological disorders and psychosomatic disorders. In total, the questionnaire consists of 33 items (23 for the reduced version), each with a 5-point scale (1 = never, 2 = rarely, 3 = sometimes, 4 = often and 5 = always). The total score is obtained by summing the points. A difference of ± 10 points with a 95% confidence interval shows significance in the variation of burnout (Daniels et al., 2022). The BAT will be the tool to assess the primary outcome for DCPs.

For the OPDs, demographic and baseline data will include age, gender, nationality, marital status, education, living condition, dementia service they attend, type of diagnosis, time of diagnosis, level of verbal expression and comprehension. As outcome tools, the following psychometric and standardized measures will be used.

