The WHO Wellbeing Index (WHO-5) is a self-assessment tool to measure the subjective mental well-being of individuals which is validated for older people (Heun et al., 1999). It includes five items each scored from 0 to 5. The total score ranges from 0 to 25, with higher scores indicating greater mental well-being. Scores < 13 indicate poor well-being and suggest depression according to the criteria of the International Statistical Classification (Tiganov et al., 1997). It is recommended to transform the raw scores to percentage scores, by multiplying it by 4, for data analysis when investigating change over time (Topp et al., 2015). Low mood may be suggested by a percentage score of ≤ 50 whilst a score of ≤ 28 may indicates depression. Similar to Kikuchi et al. (2023), a variation of ± 10 points of the percentage score with 95% confidence intervals will be considered significant. The reliability and validity of the WHO-5 is well established (e.g., Bech, 2012; Takai et al., 2013). The WHO-5 will be the tool to assess the primary outcome for OPDs.

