#### 2.4 Data analysis

The analysis plan includes, for quantitative data, outcomes description. Normality in distribution of continuous variables will be assessed via Shapiro-Wilk test and the following measures will be reported: mean and standard deviation for normally distributed variables or median and interquartile range for non-normally distributed variables. Absolute frequency and percentage will be reported for categorical variables. Comparisons between outcomes and exposures will be made using the Chi Square test, (in the case of categorical variables) or *t*-test or F-Anova (in the case of comparisons between normally distributed continuous variables and the groups), or by non-parametric tests such as Wilcoxon rank-sum test or Kruskal-Wallis test (in the case of comparisons between non-normally distributed continuous variables and the groups). Through Pearson’s or Spearman’s correlation we are going to study the relationship between continuous variables as appropriate according to variables’ distribution. Temporal comparisons (T0 vs. T1, T0 vs. T2, or T1 vs. T2) will be conducted by *T*-test for paired samples. Possible multivariate models will be assumed in case of significant differences in outcomes at the univariate level: coefficients and standard errors or odds ratios and 95% confidence intervals will be reported according to the typology of outcomes (continuous or binary). Goodness of fit will be determined by R-squared of pseudo R-squared as appropriate. Subjects withdrawing from the study will not be replaced, according to the intention to treat (ITT) principle. Sequential imputation using chained equations method will be applied in case of missing values in covariates. Statistical analyses will be conducted by a statistician, who will be blind to group allocation prior to analysis. The significance threshold will always be set at p < 0.05. The software used for the analyses will be SPSS for Win V24.0 (SPSS Inc., Chicago, IL, USA).

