The activities and music are carefully chosen in order to elicit in participants only feelings of peace and well-being, as previous similar experiments have shown (Caldini et al., 2019). In compliance with the Declaration of Helsinki (stating that “the protocol should describe arrangements for post-study access by study participants to interventions identified as beneficial in the study or access to other appropriate care or benefits”), should this study provide evidence of the effectiveness of SOUND, the SOUND activities will be included in the routine of the dementia care centers. This goal is probable and achievable because a total of 63 professionals have been trained on the SOUND method, 29 in Italy, 17 in Portugal and 17 in Romania; moreover, the Virtual Music Circle training platform is predisposed to train further professionals (Quattrini et al., under review, see text footnote 2).

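### No deciding time contrast is named for WHO-5 or BAT, while up to three paired tests per outcome, primary or secondary, are all judged at p < 0.05

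*Protocol article*

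**What the plan says.** Section 2.1 sets three assessments: T0 one week before the intervention, T1 at its end and T2 two weeks later. Section 2.2.1 plans 45 older people with dementia (OPDs) and 45 dementia care professionals (DCPs).

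Section 2.3.2 names one primary tool for each population: "The WHO-5 will be the tool to assess the primary outcome for OPDs" and "The BAT will be the tool to assess the primary outcome for DCPs". Section 2.3.1 ranks the rest as secondary; "for OPDs, they are levels of (a) cognitive abilities, (b) neuropsychiatric symptoms, (c) mood and (d) emotional well-being".

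Section 2.4 then says: "Temporal comparisons (T0 vs. T1, T0 vs. T2, or T1 vs. T2) will be conducted by" a paired t-test. The threshold follows without exception: "The significance threshold will always be set at p < 0.05". Significant univariate differences are also the condition for fitting multivariate models.

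Section 2.3.2 treats a ±10-point variation with a 95% confidence interval as significant for both WHO-5 (percentage score) and BAT, and the Discussion repeats these as expectations. Neither place says whether the change is measured at T1 or T2.

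Section 2.5 states: "should this study provide evidence of the effectiveness of SOUND, the SOUND activities will be included in the routine of the dementia care centers".

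**The concern.** A primary outcome measured three times has a 5% error rate only if one comparison is fixed as decisive. Here three are available and none is preferred. A reader of the results could take a significant WHO-5 change at T1, at T2, or between T1 and T2 as the finding, and the plan would permit each. T1 vs T2 compares two post-intervention points, yet it stands on equal terms with the comparisons against baseline.

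The ranking of outcomes in section 2.3.1 has no effect in section 2.4, where a secondary score at p < 0.05 is handled exactly as a primary one. At stake is how far a significant result can be trusted when it is used to claim efficacy, to move on to multivariate modelling, or to support adoption in the care centres.

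This is a stated rule and not a gap left to a separate analysis plan. A plan that adjusted the threshold would contradict the word used in section 2.4 to make it universal.

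**Working it through.** The article gives no familywise error figure, so there is nothing to reproduce first.

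**Inputs from the article:** threshold 0.05 (section 2.4); up to three contrasts per outcome (section 2.4); n = 45 per population (section 2.2.1). **Assumed:** two-sided tests, normal data, equal correlation between visits, no missing data, and a between-score correlation of 0 to 0.8.

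**One outcome**

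With equal visit correlation ρ and variance σ², each T0-based change has variance 2σ²(1−ρ). The two changes share the covariance σ²(1−ρ). Their correlation is therefore 0.5 whatever ρ is, and the results below barely depend on ρ.

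- *All three contrasts.* In large samples, at least one is significant when the range of three independent standard normals exceeds 1.96 × √2 = 2.77. That probability is 12.2%. Simulation of paired t-tests at n = 45 gives 12.3-12.7% with visit correlations of 0.5 and 0.7. It is 12.3-12.4% at n = 15 and n = 30, and 12.0% if the correlation decays over time (AR(1)). Three independent tests would give 1 − 0.95³ = 14.3%.
- *T0-T1 and T0-T2 only.* P(|Z1| or |Z2| > 1.96) at correlation 0.5 is 9.1%; simulation gives 9.1-9.4%.
- *Significant improvement from T0 at T1 or T2.* P(Z1 or Z2 > 1.96) at correlation 0.5 is 4.5%; simulation gives about 4.6%. One fixed contrast would give 2.5%.
- *One fixed contrast, two-sided.* 5%, confirmed by simulation.

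**Several OPD scores**

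Table 3 lists five OPD scales at T0, T1 and T2: WHO-5, MoCA, FAB, HADS and NPI. Section 2.3.2 gives the NPI two totals, symptoms and caregiver distress, which makes six scores. That is up to 5 × 3 = 15 or 6 × 3 = 18 tests. The chance of any significant result with no true change, at n = 45, is:

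| Between-score correlation (assumed) | Five scores | Six scores |
|---|---|---|
| 0 | about 48% | about 54-55% |
| 0.3 | about 45% | about 50% |
| 0.5 | about 40% | about 45% |
| 0.7 | about 33% | about 36% |
| 0.8 | about 29% | about 31% |

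The five-score column also serves for the secondary scores alone, since MoCA, FAB, HADS and the two NPI totals are five.

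**The case against.** The best defence has four parts.

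1. **Pilot status.** The article describes feasibility and preliminary outcomes ahead of a larger study, and formal multiplicity control over secondary outcomes is often not expected of a pilot. This stands as a reason not to demand a full adjustment scheme. It does not settle the primary contrast. The title speaks of checking efficacy, the abstract of investigating effectiveness, and section 2.4 uses significance as a gate to modelling.

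2. **The stated criteria are directional and sized.** Worsening, or a T1-T2 difference, would not support the expected improvement. This stands, and it is why 4.6% against 2.5% is the fairer figure for a false claim of improvement on one primary outcome. If ±10 is read as a required mean change, the chance falls further. With an assumed SD of change of 25, the standard error is 25/√45 = 3.73, and 10/3.73 = 2.68 gives under 1% over the two T0-based contrasts. With an SD of 30 it is about 2%. But the article does not say whether ±10 applies to the group or the individual, and the p < 0.05 rule stands beside it.

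3. **The text joins the contrasts with *or*.** It does not commit to running all three for every scale. That is true, but an open choice made after seeing the data carries the same risk.

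4. **The Discussion mentions pre-post evaluation with follow-up.** This hints at T0 vs T1 as the main comparison, but no sentence makes it so.

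Several stronger readings go too far:

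- A reader might infer that there is no hierarchy at all. Sections 2.3.1 and 2.3.2 do rank outcomes; what is missing is an order among time contrasts.
- A reader might infer that every outcome is tested this way. The daily thermometer (LEWT) and the per-session tools (LSET, AARS) are not T0/T1/T2 measures.
- A reader might quote 45% as the error rate across the OPD scales. That is one cell of the table: it needs six scores and an assumed correlation of 0.5, pools WHO-5 with secondaries, and counts worsening and T1-T2 differences.
- A reader might combine WHO-5 and BAT into about 23%, that is 1 − (1 − 0.127)². They belong to two populations with separate aims and need not share one error rate.
- A reader might take section 2.5 as making adoption hang on a single p-value. It is a post-study access statement that cites the Declaration of Helsinki. The fair criticism is only that it does not say what evidence would count.

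**Conclusion.** The point holds in a limited form. WHO-5 and BAT have no deciding time contrast, and a blanket 0.05 applies to each one available. For one primary outcome with no true change, the chance of any two-sided significant result is about 12-13% over three contrasts and about 9% over the two T0-based ones. The chance of a significant improvement from T0 is about 4.6%, against 2.5%. These figures are stable across sample size and visit correlation.

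The secondary scores share the same threshold despite their lower rank. The figure of roughly 29-55% over five or six OPD scores shows the scale of the problem, but it depends on a between-score correlation that the article does not give.

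The pilot label softens the point without removing it, because significance is still put to use in the plan.

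**What to change.** In section 2.4:

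- Name one deciding contrast for each primary outcome, for example T0 vs T1 for WHO-5 and for BAT, each at two-sided 0.05 within its own population. State that the ±10-point criterion refers to that contrast.
- Test T0 vs T2 only if the deciding contrast is significant, and report T1 vs T2 descriptively. Alternatively, require a significant three-level time effect before any pairwise test; with three time points this holds the family at 5%, provided that the overall test itself does.
- Report secondary outcomes as exploratory, with 95% confidence intervals and no claim of effectiveness.

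In section 2.5, say that evidence of effectiveness means the result of the two primary contrasts.

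This needs a few sentences in 2.4 and one in 2.5, with no new data or participants. The downside is that later contrasts and secondary results can no longer stand alone as significant findings. An effect that appeared only at T2 would count as supportive information and not as proof.

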#### 2.5 Ethics

This protocol and the template informed consent forms have been reviewed and approved by the responsible local Institutional Ethical Committees, as required in each participating country with respect to scientific content and compliance with applicable research and human subjects’ regulations. Any modifications to the protocol which may impact on the conduct of the study, potential benefit of the patient or may affect patient safety, including changes of study objectives, study design, patient population, sample sizes, study procedures, or significant administrative aspects will require a formal amendment to the protocol. Any amendment to the protocol will be approved by the Ethics Committees.

Each type of subject involved will be duly and comprehensively informed about the objectives of the study and the modalities of the music-type intervention, through an information sheet but also through an interview with the scientific supervisor ([name]) when requested. Older people with dementia will be provided with the informed consent and will be asked to sign it in the presence of the family caregiver and the same sheet will be given to the latter. In the information sheet, as well as during the interview, it will be emphasized that adherence to the study is completely voluntary and that it can be quit at any time without having to give any explanation. The type of intervention will be explained to both the person with mild-to-moderate dementia and their family caregivers according to a capacity approach and with full respect for the older person’s residual capacities. For the same principle, where possible, informed consent will be signed by the person with dementia and their family caregiver/legal guardian. The intervention does not anticipate any risk, discomfort or intrusion of privacy. The professionals involved will be registered healthcare practitioners with extensive experience in working with OPDs or musicians trained in dementia care and have the skills to identify and address any discomfort experienced by participants during the intervention. The participation will not require the suspension of concomitant care or interventions.

All study-related information will be stored securely at the study site. All participant information will be stored in locked file cabinets in areas with limited access. All reports, data collection, process, and administrative forms will be identified by a coded ID [identification] number only to maintain participant confidentiality. All records that contain names or other personal identifiers, such as informed consent forms, will be stored separately from study records identified by code number. All local databases will be secured with password-protected access systems. Forms, lists, logbooks, appointment books, and any other listings that link participant ID numbers to other identifying information will be stored in a separate, locked file in an area with limited access.

The scientific integrity of the study requires that the data from all SOUND sites (i.e., Italy, Portugal and Romania) be analyzed study-wide and reported as such. All results coming from the data collected through this protocol are expected to protect the integrity of the major objective of the study at the time of their dissemination through scientific papers and oral presentations, that will be agreed in the Steering Committee (made of the Authors).

The primary outcome papers of SOUND i.e., those reporting the effects of the intervention on OPDs’ wellbeing and DCPs’ burnout will be presented by the first author to the Steering Committee for approval as well as secondary outcome papers and presentations (e.g., on DCPs’ cooperation or OPDs’ reduction of neuropsychiatric symptoms). The study results will be released to the participating DCPs, OPDs, informal caregivers and the general medical community.

The activities and music are carefully chosen in order to elicit in participants only feelings of peace and well-being, as previous similar experiments have shown (Caldini et al., 2019). In compliance with the Declaration of Helsinki (stating that “the protocol should describe arrangements for post-study access by study participants to interventions identified as beneficial in the study or access to other appropriate care or benefits”), should this study provide evidence of the effectiveness of SOUND, the SOUND activities will be included in the routine of the dementia care centers. This goal is probable and achievable because a total of 63 professionals have been trained on the SOUND method, 29 in Italy, 17 in Portugal and 17 in Romania; moreover, the Virtual Music Circle training platform is predisposed to train further professionals (Quattrini et al., under review, see text footnote 2).

